### Randomization and blinding

Eligible patients will be allocated using a web-based 1:1 randomization process. The randomization will be stratified by center, and the Pocock and Simon’s minimization method will be implemented to balance two important prognostic factors, endovascular treatment and baseline NIHSS score (≥14 or < 14). The study drugs, glibenclamide and placebo, are manufactured by Succhi Pharmaceutical (Zhongshan, China) following Good Manufacturing Practices regulations, and are coded and concealed by an independent biostatistician. In this manner, all trial participants, care providers and outcome assessors will be blinded to intervention allocation.

### Treatment

An overview of the study flowchart is presented in Fig. 1. Intravenous rtPA treatment will be initiated at a standard dose and regimen (0.9 mg/kg, initial bolus of 10% of the total dose and the remaining dose as an intravenous infusion lasting over 60 min) following current clinical guidelines [14]. When a patient meets all the inclusion/exclusion criteria and signs the informed consent, randomization will be performed and the study drug will be given as soon as possible after starting the infusion of rtPA treatment. Based on previous studies, the target time from symptom onset to the start of study drug is ≤10 h [9, 15]. The study drug (glibenclamide/placebo, 2.5 mg/pill) will be evenly divided with a pill splitter and given orally by trained hospital nurses. If the patient is unable to ingest orally due to dysphagia or altered consciousness, the study drug will be grinded and dissolved with water and administered through a nasogastric tube, followed by flushing down the nasogastric tube with water. In order to achieve a steady-state concentration rapidly, a loading dose of 1.25 mg will be given, followed by 0.625 mg every 8 h for 5 days. The total given dose will be 10 mg. Since the optimal dosage of oral glibenclamide in treating AIS remains unclear, in this study we use a relatively low-dose regimen differed from that of intravenous preparations [16], with combined consideration of its high bioavailability and hypoglycemic potency. In our preliminary study, the current dose regimen of oral glibenclamide was well tolerated, associated with less brain edema, and did not increase the risks of early death, hypoglycemia, and early neurological deterioration [17]. In addition, our unpublished data has shown that this dosing regimen was able to result in average steady-state plasma glibenclamide levels of 19 ng/mL, which is not inferior to the concentrations reached by the effective therapeutic dose in rats [16].

**Fig. 1 Fig1:**
[figure not shown]
Flowchart of the trial. AIS, acute ischemic stroke; SAEs, severe adverse events; IQCODE, Informant Questionnaire on Cognitive Decline in the Elderly. *If a patient is discharged within 7 days, the examination will be performed at the day of discharge

To increase the adherence to intervention protocols, all participants will receive their study drugs at the scheduled time and take the medicine under the supervision of trained nurses. Because all subjects will receive thrombolytic therapy, for safety reasons, these patients will be hospitalized for minimum of 5 days to monitor the changes in their conditions with their complete examinations such as stroke etiology and vascular status. These all will be undertaken unless the patients voluntarily request discharge or death occurs. The patients who ask to be released from the hospital within 5 days will no longer be treated with the study drugs but will be included in the modified intent-to-treat population.

Neurological statue presented as NIHSS scores will be assessed at enrollment and at 24, 48, 72 h and 7 days. Electrocardiograms will be obtained at baseline, 6 h after the study drug administration, and at 7 days. Vital signs will be monitored frequently during the period of study drug administration. Safety lab values will be assessed at enrollment and at 24, 48, 72 h and 7 days. Cranial CT examination will be performed before randomization and repeated at 24 h, 72 to 96 h, and as clinical indicated. If a participant is discharged within 7 days, the examination will be performed at the day of discharge instead.

Since glibenclamide is an active hypoglycemic agent, blood glucose levels will be checked every 2 h during the first 24 h, followed by every 4 h in the absence of any decline below 3.9 mmol/L during the period of study drug administration. In the case of hypoglycemia, blood glucose level will be corrected by administration of glucose or glucagon, as appropriate. For safety reason, if two consecutive events of hypoglycemia (< 3.9 mmol/L) or one incidence of serious hypoglycemia (< 2.2 mmol/L) occurs, the study drug will be suspended. Blood glucose and corrective glucose administration will be reported.

Study participants will receive standard care and therapy for stroke, as well as other appropriate therapies according to clinical guidelines from the Chinese Medical Association and the American Heart Association/American Stroke Association [14, 18]. Endovascular therapy could be considered when the participant meets the criteria for endovascular therapy and operates according to the current clinical guideline [14]. Nutrition support in the form of early enteral nutrition will be initiated within 24–48 h in general, and, when indicated, parenteral nutrition will be considered, following the corresponding guidelines [14, 19]. Bolus osmotherapy is reserved for patients with clinical deterioration or radiological evidence of significant midline shift and/or mass effect. In the condition of malignant middle cerebral artery occlusion with evidence of clinical deterioration due to mass effect, indication of decompressive craniectomy will be judged by neurosurgeons but the final decision will be left to the legal representatives [20].

During the whole study period, if a suspected unexpected serious adverse reaction (SUSAR) is found, the sponsor and the principal investigator of this study have the authority and ability to unseal the patient’s intervention allocation, through the biostatistician responsible for the trial website.

### Outcome assessments

All patients will be followed up by trained neurologists blinded to study data. The primary and secondary endpoints of this study are summarized in Table 2. The SE-GRACE trial is designed with combination of clinical, imaging and biochemical outcomes to provide information about clinical benefits and relevant mechanism of action. Subjects will be followed up in person or through telephone review at 30 ± 7 days, 90 ± 14 days (the primary end-point), 180 ± 30 days and 360 ± 30 days after the onset of AIS, using modified Rankin Scale (mRS), Barthel Index (BI) and Informant Questionnaire on Cognitive Decline in the Elderly (IQCODE) (Fig. 1) [21, 22]. The primary outcome will compare the proportion of “good outcome” in the glibenclamide-treated group to the placebo group, with good outcome defined as a patient with a mRS of 0–2 at 90 days after the onset. The BI is a 10-item measure of activities of daily living which is frequently used in clinical practice and as a trial outcome measure in stroke, with a total score of 60 to 100 generally regarded as good outcome [23]. The IQCODE is an informant-based assessment tool for diagnosis of poststroke dementia and/or multidomain cognitive impairment, with a pooled sensitivity of 0.81 and specificity of 0.83 in a recent a systematic review [22]. The cutoff value of IQCODE for diagnosing poststroke dementia is generally considered to be > 3.4 [21, 22].

**Table 2 Tab2:** Primary and secondary endpoints of the trial

Outcome	Description
Primary outcome	The ratio of mRS ≤ 2 at 90 days after the stroke onset
Secondary outcome	1. The ratio of NIHSS decreased ≥4 points at 7 days after the stroke onset
	2. The ratio of parenchymal hemorrhagic transformation in cranial CT within 96 h after the onset
	3. The ratio of midline shift ≥6 mm in cranial CT within 96 h after the onset
	4. The mRS shift at 90 days after the onset
	5. The ratio of Barthel Index of 60–100 points at 90 days after the onset
	6. The proportion of Informant Questionnaire on Cognitive Decline in the Elderly (IQCODE) of ≤3.40 at 6 months and 1 year after the stroke onset
	7. The serum concentration of MMP-9 at baseline, and at 24, 48, and 72 h after onset
Safety outcome	1. The mortality at 90 days after the onset
	2. The ratio of neurological deterioration (NIHSS increased ≥4 points) within 24 h after the onset
	3. The incidence of hypoglycemia (random blood glucose < 3.9 mmol/L)
	4. The incidence of cardiac events in cardiac examination (ECG, echocardiography)
	5. The incidence of pulmonary infection
	6. The incidence of adverse event and serious adverse event

In terms of cranial CT, parenchymal hemorrhagic transformation (PH) including PH1 type and PH2 type are defined as hematoma with some space-occupying effect [24], which has been considered as a bad prognostic sign [25]. Midline shift will be measured in the section of third ventricle and categorized at 6 mm. The serum concentration of matrix metalloproteinase-9 (MMP-9) will be measured at baseline, and at 24, 48, and 72 h after the stroke onset to reflect the integrity of the blood-brain barrier [15].

Since the study will recruit AIS with NIHSS scores of 4 to 25 who are treated with intravenous rtPA, most of the included patients are severely ill and thereby most adverse events (AE) are common in this patient group irrespective of treatment strategies. AEs will be recorded on daily basis. AEs relevant to the study drug are considered to be the need for decompressive craniectomy (determined by neurosurgeons) and hypoglycemia < 3.9 mmol/L in the first 5 days. All-cause mortality, cardiac mortality, early neurological deterioration (NIHSS increased ≥4 points within 24 h of the onset) and cardiac-related and blood glucose-related AEs/SAEs will be of specific focus.

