### Patient inclusion and exclusion criteria

Eligibility criteria are presented in Table 1. Patients aged 18 to 74 years with AIS and a symptomatic anterior circulation occlusion with a deficit on the National Institute of Health Stroke Scale (NIHSS) of 4 to 25 points, treated with intravenous rtPA within the first 4.5 h of clinical onset, are eligible for participation in this trial. The exclusion criteria are modified from that set in the previous study [15]. The diagnosis of AIS is based on cranial CT scan and clinical manifestations. However, since not all patients will receive brain MRI examination or angiography before randomization, the diagnosis of anterior circulation AIS will base largely on clinical symptoms and signs, and thus some patients with posterior circulation occlusion alone may be mistakenly included before an MRI examination or angiography done. Therefore, once these subjects are diagnosed with posterior circulation occlusion alone after being included, they would stop using the study drugs immediately, but continue to receive other standard treatment and follow-up. These participants will be excluded from the modified intent-to-treat population when performing statistical analysis. Site investigators are responsible for enrolling participants, obtaining informed consent and managing randomization.

**Table 1 Tab1:** Inclusion and exclusion criteria for the SE-GRACE trial

Criteria	Description
Inclusion criteria	1. Clinical diagnosis of acute ischemic stroke in the MCA territory (PCA and/or ACA territory involvement in addition to primary MCA territory stroke is acceptable)
	2. Aged ≥18 and ≤ 74 years
	3. A baseline NIHSS score between 4 to 25
	4. Intravenous rt-PA thrombolysis conducted within 4.5 h after stroke onset, if known, or the time last seen well [termed “time last known at neurologic baseline” (TLK@B)]
	5. The time to the start of administration of Study Drug must be ≤10 h after time of symptom onset or TLK@B
	6. Informed consent was signed by the subject or the legal representative
Exclusion criteria	1. Prior to stroke, significant disability exist, with modified Rankin Scale > 1 point
	2. With medical history or evidence of cerebral hemorrhage, subarachnoid hemorrhage, arteriovenous malformation, cerebral aneurysm or brain tumor
	3. With clinical or imaging evidence of contralateral cerebral infarction which is believed to have influence on the patient outcome by the investigators

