### Statistical analyses

The primary outcome will be compared between 2 groups using χ^2^ tests, and the confidence interval of the rate difference will be calculated using the Newcombe’s method [27]. Common risk difference for multiway 2 × 2 tables stratified by endovascular treatment and baseline NIHSS score (≥ 14 or < 14) will also be reported. The Mantel-Haenszel estimate, confidence limits, and test for the common risk differences by using Mantel-Haenszel stratum weights and the Sato variance estimator will be used. When half of the planned subjects are recruited and their 90-day follow up are finished, interim analysis will be conducted by a selected biostatistician. O’Brien - Fleming method will be used to control the Type I error. The trial will be stopped early when the primary outcome of the interim analysis significantly favors or contradicts the usage of glibenclamide.

For baseline variables and other outcomes, comparisons between normally distributed continuous variables, expressed as mean ± SD, will be performed using 2-sample t tests; non-normally distributed continuous variables, presented as median and interquartile range, will be analyzed using Wilcoxon rank sum tests. Pearson χ^2^ or Fisher exact tests will be used, as appropriate, for categorical data, which will be expressed as percentages. For secondary outcomes mRS shift and MMP-9, mixed effect model will also be used.

For safety analysis, all adverse events and serious adverse events, including deaths, will be summarized by body systems in terms of frequency, severity, and relatedness to the study drug using the MedDRA codes. Frequencies of adverse events from these two groups will be reported. Pearson χ^2^ or Fisher exact tests will be used, as appropriate, to compare the incidence of adverse events between the two groups.

Subgroups analyses will be performed according to pre-defined design variables, such as: sex, age (≤ 60 years vs. 61–74 years), endovascular treatment, NIHSS grade (4–13 vs. 14–25), time window in rtPA thrombolysis (< 3.5 h vs. 3.5–4.5 h), and study drug treatment time (< 6 h vs. 6–10 h).

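### The day-7 NIHSS responder rule demands near-complete recovery from patients entering at 4 or 5, and its unadjusted test loses roughly half the information under assumed distributions

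*Protocol article*

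**What the plan says.** Table 2 of the Protocol article lists secondary outcome 1 as "The ratio of NIHSS decreased ≥4 points at 7 days after the stroke onset". It offers no second route to response, such as reaching a score of 0 or 1. Inclusion criterion 3 in Table 1 is "A baseline NIHSS score between 4 to 25".

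The Treatment section schedules the score repeatedly: it "will be assessed at enrollment and at 24, 48, 72 h and 7 days". For early leavers it adds: "If a participant is discharged within 7 days, the examination will be performed at the day of discharge instead".

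Under Statistical analyses, "Pearson χ^2^ or Fisher exact tests will be used, as appropriate, for categorical data". The same paragraph then names the outcomes that also receive a model: "For secondary outcomes mRS shift and MMP-9, mixed effect model will also be used". NIHSS is not among them. The Mantel-Haenszel analysis stratified by endovascular treatment and NIHSS (14 or more, or below 14) is described for the primary outcome.

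The Randomization and blinding section names baseline NIHSS as one of two important prognostic factors and minimizes on it at 14. Subgroups of 4–13 and 14–25 are pre-defined.

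**The concern.** A fixed drop of 4 points does not mean the same thing across an entry range of 4 to 25. At the bottom it demands complete or near-complete recovery; at the top a modest change is enough. The responder rate is therefore partly a description of how severe the recruited patients were, which makes it hard to interpret or to compare with other cohorts.

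The test also discards detail that the trial collects. The score is reduced to yes or no, and the comparison does not adjust for the baseline value that the trial itself treats as prognostic. For mRS the article plans both a dichotomy and a shift analysis; for NIHSS it lists only the dichotomy. This is the only early clinical efficacy outcome in Table 2: the other early secondary outcomes are CT findings and serum MMP-9, and the 24-hour NIHSS rise is a safety outcome.

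**Working it through.** **1. The plan's own figure.** The article states no power, sample size or expected rate for the NIHSS outcome. Its only size calculation is for the primary outcome, and it reproduces:
- 41% vs 58%, two-sided 0.05, power 80%, no continuity correction: 135 per arm.
- Two-look O'Brien-Fleming spending, inflation 1.0087: 135 × 1.0087 = 136.2, so 137.
- Dropout 10%: 137 / 0.9 = 152.2, so 153 per arm and 306 in total, as stated.

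About 153 × 0.9 ≈ 138 per arm (276 in total) would be analysed. The checks below use that number.

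**2. What the rule requires.** From the article's own threshold and entry range, a patient with baseline *b* counts if the day-7 score is at most *b* − 4, a drop of 4/*b*.

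| Baseline | Highest day-7 score that counts | Drop required |
|---|---|---|
| 4 | 0 | 100% |
| 5 | 1 | 80% |
| 6 | 2 | 67% |
| 8 | 4 | 50% |
| 14 | 10 | 29% |
| 25 | 21 | 16% |

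A patient going from 5 to 2 (a 60% drop) fails, and one going from 24 to 20 (17%) succeeds. This step needs no assumption.

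**3. Information kept, by formula.** Assume baseline and day-7 scores are bivariate normal with equal SDs and correlation ρ, and let *q* be the responder share. The efficiency of the dichotomised change relative to ANCOVA is φ(z_q)² / [q(1 − q)] × (1 + ρ)/2.
- Lowest: q = 0.3 or 0.7, ρ = 0.4: 0.576 × 0.7 = 0.403.
- Highest: q = 0.5, ρ = 0.8: 0.637 × 0.9 = 0.573.

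Over ρ = 0.4, 0.6, 0.8 and q = 0.3, 0.5, 0.7, the responder test keeps 40–57% and loses 43–60%. The loss exceeds half in 5 of 9 cases.

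**4. Information kept, by simulation.** Assumptions:
- Three baseline shapes on 4–25: uniform, centred near 12, and right-skewed.
- Day-7 score equal to baseline less 30% or 45%, with a further 10 percentage points on treatment.
- Noise SD of 3 or 5 at baseline 12, growing with baseline; scores rounded and bounded at 0. No deaths.

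Over 12 settings with 1,500 trials each:
- Relative efficiency of the responder chi-square against ANCOVA was 0.22–0.57, a loss of 43–78%. The loss exceeded half in 8 of 12.
- Power was 22–62% for the responder test and 39–94% for ANCOVA.
- Placebo response was 15–34% at baseline 4–5 and 60–90% at 14 or more.
- Patients entering at 4–5 made up 5–16% of the assumed cohorts.

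**5. The analysis recommended below, with deaths.** Comparing the responder test with rank ANCOVA at 138 per arm, under two assumed baseline shapes and proportional or constant effects, the adjusted analysis gained 14–26 power points without deaths. With about 5% early deaths ranked worst it gained 10–20. Type I error was held. A separate run with 6% early deaths, equal in both arms, gave gains of 1–23 points once a model in which only a subset of patients benefits was included. The adjusted analysis was never the less powerful.

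**The case against.** The strongest reply is that nothing here is misstated or contradictory. A 4-point step is a usable responder definition, and the article uses the same step for neurological deterioration. The outcome is already a change from baseline, so baseline is not ignored. The article makes no power claim for it. All of this stands, and it is why the responder proportion should be kept.

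The floor problem bites mainly at entry scores of 4 and 5, perhaps a small share of patients, and the article expects most patients to be severely ill. That limits the size of the problem but does not remove the efficiency loss, which applies across the whole range.

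The article is also a condensed document. A rationale for the cut, or a supportive NIHSS analysis, may sit in the full protocol or SAP, so the lack of a stated reason is not held against it. What the article does fix is the endpoint, the unadjusted test, and a list of modelled outcomes that leaves NIHSS out.

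A reader might infer that dependence on baseline severity biases the comparison. It does not: the rule applies equally in both arms, and minimization limits imbalance in NIHSS. A reader might also infer that the responder outcome should be replaced. Replacing it would be debatable; adding an adjusted analysis is enough.

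**Conclusion.** The point holds as a loss of efficiency and interpretability on one secondary outcome. That response means full or nearly full recovery at NIHSS 4–5 and a 16% drop at 25 follows from the article's own figures.

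The size of the efficiency loss rests on assumed distributions, variability and effects, because the article gives none. Roughly half of the information is a fair summary. It is tempting to say that most is lost, but the loss exceeded half in only 5 of 9 analytic and 8 of 12 simulated cases. For power, the relevant figures are those that include deaths, since the recommended analysis ranks them: about 10–20 points with about 5% early deaths, against 14–26 without, and as little as 1 point under less favourable effect models.

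**What to change.** Keep the proportion with a drop of at least 4 points in Table 2. In Statistical analyses, pre-specify one baseline-adjusted analysis of the full-scale day-7 NIHSS, before unblinding. For example:

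*Day-7 NIHSS will also be compared between groups by rank ANCOVA with baseline NIHSS as covariate. Patients who die before day 7 receive the worst rank. For patients discharged earlier, the score on the day of discharge is used.*

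The last sentence reads the article's early-discharge provision as covering the NIHSS; the text should say so. One method should be named, not a choice of several. If the SAP already contains such an analysis, the article needs only a sentence pointing to it.

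The cost is small: no new visits, data or patients. It does add one secondary analysis, a rule for ranking deaths, and an effect summary less familiar than a responder rate, which is still reported beside it.

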### Sample size estimation

The sample size calculation was based on previous findings, and the proportion of patient with a mRS of 0–2 at 90 days of 41% was estimated for the placebo group, and of 58% was assumed for the glibenclamide-treated group [11]. When half of the planned subjects finish their 90-day follow up an interim analysis will be conducted and the O’Brien - Fleming method will be used to control the type I error. Using nQuery + nTerim 4.0 (Statistical Solutions Ltd., Farmer’s Cross, Cork, Ireland) with a 2-sided χ^2^ test, a two-sided significance level of 0.05, a power of 80%, the O’Brien - Fleming alpha spending function and a dropout rate < 10%, 153 patients are required in each group, for a total sample size of 306.

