The primary and secondary end points will be analyzed based on the modified intention-to-treat (mITT) population which excludes those patients who do not receive treatment or control and has no efficacy outcome data, and those subjects who are diagnosed with posterior circulation occlusion alone after being included. Per-protocol patients who finish the treatment protocol with good compliance, will also be analyzed as a sensitive analysis. Safety analyses will be done in patients receiving allocated treatment. Last observation carried forward method will be used to deal with the missing data of primary outcome, and multiple imputation method will also be used as sensitive analysis. All analyses will be 2-tailed and a significance level of 0.05 will be used for all outcomes. All data analyses will be performed using SAS version 9.4 (SAS Institute, Cary, NC).

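### Baseline MMP-9 is listed as part of an outcome, and unadjusted MMP-9 tests stand unranked beside a mixed model; using baseline as a covariate is a free gain in precision

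*Protocol article*

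**What the plan says.** - **Endpoint.** Protocol article, Outcome assessments, Table 2, secondary outcome 7: "The serum concentration of MMP-9 at baseline, and at 24, 48, and 72 h after onset". The text after the table gives the same four times as a sampling plan, saying that MMP-9 "will be measured at baseline, and at 24, 48, and 72 h after the stroke onset to reflect the integrity of the blood-brain barrier".
- **Default tests.** The Statistical analyses section sets one rule for baseline variables and all outcomes other than the primary. Normally distributed continuous variables, "expressed as mean ± SD, will be performed using 2-sample t tests". Non-normal ones, "presented as median and interquartile range, will be analyzed using Wilcoxon rank sum tests". Neither test takes a covariate, and MMP-9 falls under this rule.
- **Additional model.** The same section adds: "For secondary outcomes mRS shift and MMP-9, mixed effect model will also be used".
- **Error level.** "All analyses will be 2-tailed and a significance level of 0.05 will be used for all outcomes".

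The article does not rank the default tests against the mixed model for MMP-9, and it names no main time point or contrast.

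**The concern.** Two printed items cause the difficulty.

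First, the endpoint includes a value taken before treatment. As a sampling schedule the four times are sensible. As an outcome, the baseline value can show only chance imbalance between the arms. Listing it there also invites a model that treats baseline as one more response, with its own mean in each arm.

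Second, the default tests ignore the baseline value even though it is collected. Because the mixed model is an addition, the unadjusted tests remain planned analyses of equal standing. Read literally, the plan gives a test at each time point plus a model, all at 0.05, and does not say which one answers the MMP-9 question.

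At stake is the precision and clarity of the only serum marker in Table 2, which the article presents as reflecting blood-brain-barrier integrity.

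**Working it through.** **1. The plan's own figure.** The article gives no SD, effect, correlation or power for MMP-9. The only figure to reproduce is the sample size in Sample size estimation ("mRS of 0–2 at 90 days of 41% was estimated for the placebo group"; 58% on glibenclamide; two-sided 0.05; 80% power; one interim look at half the subjects with O'Brien–Fleming spending; dropout below 10%).
- χ² formula: [1.960·√(2·0.495·0.505) + 0.842·√(0.41·0.59 + 0.58·0.42)]² / 0.17² = 134.6, so 135 per arm.
- Interim inflation factor 1.0087: 135 × 1.0087 = 136.2, so 137.
- Dropout: 137 / 0.90 = 152.2, so 153 per arm and 306 in total. This matches the article.

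If the same 10% loss applied to MMP-9 samples, 153 × 0.90 = 137.7, so about 138 per arm would be evaluable. That is an assumption.

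**2. Gain from baseline as a covariate, one follow-up time.** In large samples, the variance of the adjusted contrast relative to the unadjusted one is 1 − r². The correlation r is not in the documents, so a range is shown. The 80% starting power is for illustration only.
- Power after adjustment = Φ(2.802/√(1 − r²) − 1.960). At r = 0.5: 2.802/0.866 = 3.235; 3.235 − 1.960 = 1.275; Φ = 0.90.
- Difference detectable with 80% power, 138 per arm, in SD units = 2.802·√(2/138)·√(1 − r²) = 0.337·√(1 − r²).

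| Assumed r | Variance ratio | Power, if 80% unadjusted | Detectable difference (SD) |
|---|---|---|---|
| 0 | 1.00 | 80% | 0.337 |
| 0.3 | 0.91 | 84% | 0.322 |
| 0.5 | 0.75 | 90% | 0.292 |
| 0.7 | 0.51 | 97.5% | 0.241 |

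**3. Would the planned mixed model recover this?** The article does not give its terms, so the plausible forms were simulated: 1,500 runs, 138 per arm, four time points with equal variances and a common correlation r. The table shows the variance of the 72 h contrast relative to the unadjusted comparison.

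| Analysis | r = 0.3 | r = 0.5 | r = 0.7 |
|---|---|---|---|
| Baseline as covariate (ANCOVA) | 0.91 | 0.77 | 0.50 |
| Mixed model, baseline a response, common baseline mean | 0.91 | 0.77 | 0.50 |
| Mixed model, separate baseline means by arm, level contrast at 72 h | 1.00 | 1.00 | 1.00 |
| Same model, change-from-baseline contrast | 1.33 | 1.07 | 0.57 |

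The first two rows agree with 1 − r² within simulation error. The last row agrees likewise with its theoretical value 2(1 − r), which is 1.40, 1.00 and 0.60. So the mixed model recovers the whole gain in one form and none of it in another, and with the change contrast it can do worse than the unadjusted test when r is below 0.5.

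**The case against.** The strongest reply is that the article does plan a longitudinal model for MMP-9 by name, and that model may already use baseline well. A condensed article commonly leaves model terms to the full protocol or SAP, which are not shown, so their absence is not a fault. The list in Table 2 can also be read as a sampling schedule, since the text below it says when MMP-9 is measured. And randomisation makes the unadjusted tests valid.

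Most of this stands, and it rules out three stronger readings that a reader might infer:
- **That the plan ignores baseline and certainly wastes precision.** Not supported. The mixed model is planned, and the check above shows that one ordinary form of it matches ANCOVA.
- **That a constant effect would be diluted by a quarter**, by averaging one null baseline value with three follow-up values. This needs both baseline as a response and a treatment main effect as the reported result. The article states neither. Having baseline among the responses is not an error in itself.
- **That the unadjusted comparison is biased by baseline imbalance.** Chance imbalance is already reflected in the standard error. The cost is precision, not bias.

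What the reply does not remove is the printed text. Table 2 lists baseline within an outcome, the default tests for that outcome are unadjusted, and the model is added beside them without either being named as the main analysis.

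**Conclusion.** The point holds as a free improvement of low severity. Baseline MMP-9 should not be part of an outcome, and the stated unadjusted tests forgo a possible reduction in variance of 9%, 25% or 49% at r of 0.3, 0.5 or 0.7, and none at r = 0. Whether the plan as a whole loses this depends on how its mixed model uses baseline, which the article does not say.

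The sizes rest on an assumed r, large samples and a roughly linear relation on the scale analysed. The power column also rests on an arbitrary 80% start. For the Wilcoxon test the ratios are only a guide. MMP-9 is the last of seven secondary outcomes. The primary analysis and the sample size of 306 rest on the 90-day mRS and do not change.

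**What to change.** - In Table 2, define secondary outcome 7 as serum MMP-9 at 24, 48 and 72 h after onset. Keep the baseline sample in the measurement schedule.
- In Statistical analyses, name the planned mixed effect model as the main MMP-9 analysis, with baseline MMP-9 as a covariate (or, equivalently, baseline as a response with a common mean across arms), treatment, time and treatment-by-time.
- Keep the t or Wilcoxon comparisons of MMP-9 as descriptive or supportive only.
- Optional, as a matter of preference: analyse on a log scale, and prespecify the average contrast over 24 to 72 h as the single MMP-9 result. The article gives no MMP-9 distribution, and an average suits an effect that is fairly constant over time.

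Cost: wording only. All four samples are already planned, and no extra patients, visits or assays are needed. If the full protocol or SAP already specifies this, only the Table 2 entry and the ranking of the analyses need to be aligned with it.
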